### Participants

#### Inclusion criteria

Able to speak and read English, Spanish, Korean, or JapaneseBiopsy-confirmed diagnosis of non-metastatic gastric or GEJ adenocarcinoma scheduled to undergo curative-intent MIPG or MITGAge ≥ 18

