## Background

The current standard surgical procedure used to treat proximal gastric and gastroesophageal junction (P/GEJ) cancers with limited esophageal extension is total gastrectomy (TG), unless the tumor is small (< 3 cm in diameter) and contained in the mucosal layer (pT1a); such tumors can be removed via endoscopic mucosal resection [1]. TG is associated with impaired appetite and weight loss [2–4] due to the loss of gastric functions such as production of ghrelin (the “hunger hormone” secreted by the stomach) [5] and with anemia due to intrinsic factor loss and vitamin B_12_ malabsorption. Theoretically, proximal gastrectomy (PG) can mitigate these problems by preserving gastric function. However, PG with direct esophagogastric reconstruction is associated with severe postoperative reflux and poor quality of life (QoL) and is therefore rarely performed in Western countries, including the United States [6, 7]. The lack of an effective surgical procedure that preserves gastric function and postoperative QoL for patients with P/GEJ cancers is a critical gap.

With the recent development of effective post-PG anti-reflux reconstruction techniques, such as double-tract reconstruction and the double-flap technique, PG has been increasingly used to treat proximal gastric cancer in South Korea and Japan [8–13]. Researchers in the KLASS-05 trial (NCT02892643) have recently reported results comparing outcomes at 2 years after PG with outcomes at 2 years after TG in patients with cT1N0 proximal gastric cancer, and these results showed that PG reduced the need for vitamin B_12_ supplementation and improved some QoL measurements. However, it remains unknown whether PG with double-tract reconstruction or the double-flap technique has short-term postoperative QoL advantages over TG [8, 12, 13]. In addition, the theoretical disadvantages of PG include incomplete lymph node (LN) removal, which may result in recurrence, and the potential for a second gastric cancer in the remnant stomach. Moreover, delayed gastric emptying of the remnant stomach can cause upper gastrointestinal symptoms such as reflux and bloating. The QoL benefits of PG must therefore be clearly demonstrated before encouraging its use in Western countries.

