PG is commonly indicated for cT1 proximal gastric cancer in South Korea and Japan [8–13], with reported excellent overall and recurrence-free survival. Given the low incidence of LN metastasis in cT1 gastric cancers, PG is considered safe for cT1 proximal gastric cancer. A recent Japanese prospective study of GEJ adenocarcinoma reported a low incidence of LN metastasis at peripyloric stations (suprapyloric [station 5] and infrapyloric [station 6]) regardless of tumor stage [14], and surgeons thus began performing PG for GEJ cancers in Eastern Asia. As a result, Japanese Gastric Cancer Treatment Guidelines now recommend PG as a surgical option for GEJ cancers with limited esophageal extension [15]. In Western countries, although TG is considered the standard surgical procedure for P/GEJ cancers, Ivor Lewis esophagectomy, which uses the gastric conduit for reconstruction [16], is also commonly performed for GEJ cancers, suggesting that PG may also be oncologically safe for GEJ cancers. However, internationally and nationally, controversy remains as to whether and when PG is oncologically safe for GEJ cancers and whether PG provides better QoL than TG [6, 7]. An international collaboration is warranted to determine the benefits and safety of PG for P/GEJ cancers and thus standardize surgical care for patients with these cancers.

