## Methods/design

This is a multicenter, open-label, prospective cohort study comparing outcomes of MIPG (trial procedure) and MITG (standard of care, control group). We expect to enroll a total of 60 patients in this study (30 per group). Patients will be recruited from and treated at MD Anderson Cancer Center, Mayo Clinic, Memorial Sloan Kettering Cancer Center, Yonsei University, and Keio University, after Institutional Review Board approval for each institution. We plan to enroll at least 20 patients each from Asian (Keio University and Yonsei University) and US (MD Anderson, and Mayo Clinic Minnesota, and Memorial Sloan Kettering Cancer Center) institutions. The total study duration is expected to be 60 months (including enrollment and follow-up). We will prospectively collect PROs longitudinally for a 1-year period. Other clinical factors will also be collected to investigate factors associated with improved PROs.

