#### Details of surgery

After adequate preoperative evaluation, patients who are judged to be physiologically capable of undergoing resection, viewed as having resectable lesions, and without evidence of metastatic disease will undergo MITG or MIPG as per their choice and the surgeon’s discretion. We do not consider randomization feasible because patients often have strong preferences regarding MITG and MIPG. After MITG, a Roux-en-Y reconstruction is performed, whereas after MIPG, an anti-reflux reconstruction technique is chosen by the surgeon (double-tract reconstruction [17] or the double-flap technique [18]) (Fig. 2). All participating surgeons need to have performed at least 30 robotic gastrectomies before enrolling patients into the study, and at least 10 of these procedures need to have used the specific type of reconstruction technique (e.g., double-flap reconstruction after proximal gastrectomy) that the patient will receive. Details of the reconstruction techniques are determined by the surgeon. Patients will undergo standard postgastrectomy care at each institution during their hospital stays. A feeding jejunostomy can be placed for postoperative nutritional support at the surgeon’s discretion. These surgical procedures can be performed with a laparoscopic or robotic approach. Patients who undergo conversion to open laparotomy will be excluded from the study analyses, since conversion is expected to impact postoperative recovery. Patients who are found to have metastatic disease during surgery will also be excluded from the study analyses, regardless of whether the patient completed gastrectomy or not. Those excluded from the study analyses will be considered screening failures to allow for additional enrollees to meet the accrual target.

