### Statistical methods

The primary outcome is appetite level score (with 0 being the best and 10 being the worst) according to the MDASI-GI + (Question #8) at 3 months after surgery. We will enroll a total of 64 patients in order to have 60 evaluable patients at 3 months after surgery (i.e., assuming a 5% attrition rate). With 30 patients expected in each cohort, this study will have 80% power to detect a one-point difference in appetite level score using a two-sample *t*-test with a 5% significance level and assuming a common standard deviation of 1.35 (nQuery Advisor 7.0). We will also compare serum ghrelin levels at 3 months after surgery. For the primary analyses, we will apply the inverse probability treatment weights using propensity scores for assessing the difference between the two surgical groups. Inverse probability weighting is applied by weighting the outcome measures by the inverse of the probability of an individual with a given set of covariates being assigned to their treatment (i.e., propensity score). The propensity scores will be derived through fitting a multiple logistic regression model with MIPG (vs. MITG) as the outcome variable. Then, in the presence of measured confounders, we can estimate the difference between the two treatment groups via inverse probability weighting of the study subjects. For the regression analyses described below for assessing the “surgical procedure” effect, the inverse probability treatment weights using propensity scores will be applied as appropriate in addition to any standard statistical methods. The two-sample t-test or Wilcoxon rank-sum test will also be used to compare the appetite level or ghrelin level at 3 months, as well as the percent change from baseline, between the two cohorts. We will longitudinally collect PROs (using the fully translated MDASI-GI +) and compare specific items and overall scores as well as body weight, body mass index, and albumin and hemoglobin levels at 1, 3, 6, and 12 months after surgery in the cohorts. A linear mixed effects model will be fit to assess the change in QoL over time while accounting for potential intra-patient correlations. “Time” points will be included as a fixed effect, and “patient” will be included as a random effect. The surgical procedure received and use of adjuvant or neoadjuvant therapy will be included as covariates. Similar analyses will be performed to assess the changes in body weight, body mass index, and albumin and hemoglobin levels over time. The number of LNs examined pathologically, incidence of postoperative complications, operating room time, blood loss, and length of hospital stay will be compared. Continuous variables (such as length of hospital stay) will be assessed using the two-sample t-test or Wilcoxon rank-sum test. Categorical variables (such as type and severity of complications) will be assessed using Fisher’s exact test. Local–regional recurrence-free and overall survival will be estimated using the Kaplan–Meier method, and Cox regression analyses will be performed to assess the association with patient characteristics and surgical procedure received. The 3-year loco-regional recurrence rate will be estimated along with the 95% confidence interval. Missing data will be excluded from analysis and no missing data imputation will be performed. Sensitivity analyses to investigate factors associated with PRO scores, including but not limited to country (west vs. east), tumor location, types of reconstruction after PG, use of neoadjuvant and adjuvant therapy, use of jejunostomy or nutrition status, on PRO scores will be performed.

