This proposal is novel because it is the first international collaborative study as well as the first American study to prospectively investigate the benefits of MIPG with anti-reflux techniques. The research is culturally innovative because we will focus on PRO as the primary outcome, thus promoting a growing appreciation of the importance of patient-oriented care in the field of surgical oncology [24]. Theoretical benefits of PG, such as an improved hemoglobin level and reduced weight loss, become clinically significant only when QoL is improved, which can only be measured using PROs. The primary endpoint (appetite level) will be serologically validated with ghrelin level, which is an appetite-stimulating hormone that is known to decrease after TG [5]. Expected confounding factors that would affect postgastrectomy PROs, such as use of neoadjuvant therapy and different types of reconstruction after PG, will be carefully analyzed in sensitivity analyses. In addition, our study will determine the safety and feasibility of MIPG (including using a robotic approach) in the international setting. This transpacific collaboration between high-volume academic cancer centers will establish the foundation for future larger trials in the field of gastric cancer surgery.

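### Eligibility does not require that a control could have had MIPG, so the weighted primary comparison lacks overlap for some MITG patients

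*Protocol article*

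**What the plan says.** The Abstract, Background and Rationale frame the question around proximal gastric and GEJ cancers with limited esophageal extension. The Inclusion criteria are wider. They require a biopsy-confirmed "diagnosis of non-metastatic gastric or GEJ adenocarcinoma scheduled to undergo curative-intent MIPG or" MITG, and set no limit on tumour location, stage or suitability for both operations. The Exclusion criteria do not narrow this.

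Assignment is not randomised. Under Details of surgery, patients "will undergo MITG or MIPG as per their choice and the surgeon’s discretion". Methods/design expects 30 patients per procedure and adds a regional floor: "We plan to enroll at least 20 patients each from Asian (Keio University and Yonsei University) and US" institutions. It sets no number per procedure within a region.

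Under Statistical methods, the primary analysis weights patients by the inverse of a propensity score from a logistic model of MIPG versus MITG. The covariates of that model are not named. Later in the same section come "Sensitivity analyses to investigate factors associated with PRO scores, including but not limited to country (west vs. east), tumor location" and further items. The Discussion says that expected confounders, "such as use of neoadjuvant therapy and different types of reconstruction after PG, will be carefully analyzed in sensitivity analyses".

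**The concern.** Inverse-probability weighting compares like with like only if every analysed patient had a real chance of either operation. The entry rule works against this in one direction. A non-proximal or extensive gastric tumour scheduled for MITG is eligible and counts towards the 30 controls, although no comparable patient could appear in the MIPG group. For such controls the comparison is between tumours as much as between procedures. If they have worse appetite for reasons tied to their disease, MIPG looks better than it is. An analysis plan cannot create the missing counterparts. It can only exclude these patients, and for that their suitability must have been recorded.

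Two further features weaken the comparison. Nothing ensures that both procedures occur in each region. And the wording on confounders points to sensitivity analyses, which do not correct the primary estimate.

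**Working it through.** **1. The planned figure.** Inputs from Statistical methods: 30 per cohort, a 1-point difference, SD 1.35, two-sample t-test at 5% (read as two-sided).
- Standard error = 1.35 × √(2/30) = 0.349.
- Noncentrality = 1/0.349 = 2.87, with 58 degrees of freedom.
- Power from the noncentral t = 80.5%. The stated 80% reproduces, but for an unweighted test.

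**2. Controls who could not have had MIPG.** Neither their number nor their outcome is given, so both are assumptions.
- Shift in the unadjusted difference = share of such controls × their appetite deficit.
- One control of 30 with a 1.5-point deficit: 1/30 × 1.5 = 0.05 points.
- Six of 30 (20%) with a 1-point deficit: 0.20 × 1 = 0.20 points.
- Six of 30 with a 1.5-point deficit: 0.20 × 1.5 = 0.30 points.

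Putting suitability into the propensity model does not remove the shift. Take 30 MIPG, 24 suitable MITG and 6 unsuitable MITG patients.
- Among the 54 suitable patients the MIPG weight is 54/30 = 1.8 and the MITG weight is 54/24 = 2.25. Each suitable group sums to 54.
- The six unsuitable controls have MIPG probability 0 and weight 1/(1 − 0) = 1, summing to 6.
- They make up 6/60 = 10% of the weighted control mean and none of the MIPG mean.
- With a 1.5-point deficit, 0.10 × 1.5 = 0.15 points remain.

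**3. Region.** Thirty Asian patients all on MIPG and 30 US patients all on MITG would meet every stated target. The weights would then be undefined. For less extreme splits (assumed), take 30 Asian and 30 US patients with region as the only covariate. The effective sample size is (Σw)²/Σw², with w the inverse probability of the procedure received. At 80/20 the MIPG group has 24 patients with w = 1.25 and 6 with w = 5, so Σw = 60, Σw² = 37.5 + 150 = 187.5, and 3600/187.5 = 19.2.

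| MIPG share, Asia/US | Effective size per group | Power with weighting | Bias per 1-point regional difference if region is not in the weights |
|---|---|---|---|
| 50/50 | 30.0 | 80.5% | 0 |
| 70/30 | 25.2 | 73.1% | 0.40 |
| 80/20 | 19.2 | 60.8% | 0.60 |
| 90/10 | 10.8 | 37.4% | 0.80 |
| 100/0 | none | undefined | 1.00 |

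A milder case, with 20 of 30 MIPG and 10 of 30 MITG patients from Asia, gives a bias of (20/30 − 10/30) × R = 0.33R for a regional difference of R points. This too applies only if region is not in the weights.

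**4. Where confounders are placed.** The Discussion names neoadjuvant therapy and reconstruction type as expected confounders and sends them to sensitivity analyses. Statistical methods names country and tumour location in its sensitivity list. It also puts adjuvant or neoadjuvant therapy into the longitudinal mixed model, but that model is not the 3-month primary contrast. Reconstruction choice exists only within MIPG, because MITG is always followed by Roux-en-Y. It therefore distinguishes versions of one treatment and cannot confound MIPG against MITG.

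**The case against.** Several points count for the plan, and some stronger readings go too far.

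- **Eligibility agrees with the stated objective.** Study objectives refers to gastric and gastroesophageal adenocarcinoma without restriction. That is so, but a broad objective does not supply MIPG counterparts for tumours that MIPG cannot treat.
- **Patients choose.** If choice and preference drive the operation, many patients presumably had both options. This stands for many. It does not show that every control had both.
- **A reader might infer that country and tumour location are left out of the propensity model.** The document does not say so. The covariates are unlisted, a factor can be in both the weights and a sensitivity analysis, and the list may sit in a document not shown. Its absence here is no fault.
- **A reader might infer that PG is rare in the West, so region will determine procedure.** The words "is therefore rarely performed in Western countries, including the United States" refer to PG with direct esophagogastric reconstruction, which is not the study procedure. The Background does say "PG is commonly indicated for cT1 proximal gastric cancer in South Korea and Japan" and calls TG the Western standard, so imbalance is plausible. But the Discussion presents this as an American study of MIPG too, so the complete 30/30 split is an extreme case and not a forecast.
- **A reader might conclude that the study cannot isolate the procedure effect.** That follows only if overlap is absent or key factors are omitted. With partial overlap, weighting still works, at a cost in power.
- **The magnitudes rest on assumptions.** This stands. The 1.5-point deficit is larger than the planning SD of 1.35.

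**Conclusion.** The point holds on eligibility. The inclusion rule admits controls for whom MIPG may never have been possible, and the weighted primary comparison has no overlap for them. Neither the propensity model nor a later analysis plan can repair this while those patients remain in the primary set.

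The regional gap and the Discussion's wording on confounders are supporting points. Overlap by region is not secured, and the document does not commit expected confounders to the primary weights. That is weaker than saying they are excluded.

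The document does not determine the size. The shifts of 0.05 to 0.30 points, the 0.33R regional bias and the drop in power to about 73% or 61% illustrate what assumed shares, deficits and splits would do against a 1-point target.

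**What to change.** 1. Restrict eligibility, or at least the primary analysis set, to proximal/GEJ tumours for which the surgeon records before surgery that either procedure was possible. Tumour location, Siewert class and esophageal extension are already on the data list in Additional clinical data, but only if available in the medical record, so they should be recorded at entry.
2. State that expected confounders enter the primary weights and not only sensitivity analyses. Keep the list short for 30 patients per group, for example region, tumour location/extension, neoadjuvant therapy and baseline appetite. A long list would make the weights unstable.
3. Pre-specify an overlap check and report the effective sample size per group with the primary result.
4. Monitor procedure by region during accrual. Fixed minimums per cell are a debatable trade-off when patients choose their operation, because they could make enrolment selective.
5. Correct the Discussion so that reconstruction type is a descriptive factor within MIPG and not a confounder of MIPG versus MITG.

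The cost is protocol wording and one pre-operative data item. The downsides are a narrower MITG group, somewhat slower accrual, and an effective sample size below 30 per group if regional overlap is poor. The suitability record has to start while patients are being enrolled, because it cannot be reconstructed reliably afterwards.

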#### Exclusion criteria

Known malabsorption syndrome or a lack of physical integrity of the upper gastrointestinal tractKnown narcotic dependence, with average daily dose > 5 mg oral morphine equivalentUnable to comply with study and/or follow-up procedures, deemed as such at investigators’ discretionPregnant (thus excluded from receiving MIPG or MITG)

#### Recruitment

After being screened for inclusion and exclusion criteria, the potential participants will be verbally introduced to the study by investigators. Each participant will sign a written informed consent form before enrollment into the study. A copy of the signed consent form will be given to the participant, and the original consent form will be kept in the system at each hospital.

### Interventions

#### Preoperative evaluation

Within 30 days prior to surgery, PRO collection will be completed using the MDASI-GI + (Fig. 1). This can be done by paper or electronic-based communication (REDCap).

**Fig. 1 Fig1:**
[figure not shown]
M. D. Anderson Symptom Inventory – Gastrointestinal Cancer (MDASI-GI +)

#### Details of surgery

After adequate preoperative evaluation, patients who are judged to be physiologically capable of undergoing resection, viewed as having resectable lesions, and without evidence of metastatic disease will undergo MITG or MIPG as per their choice and the surgeon’s discretion. We do not consider randomization feasible because patients often have strong preferences regarding MITG and MIPG. After MITG, a Roux-en-Y reconstruction is performed, whereas after MIPG, an anti-reflux reconstruction technique is chosen by the surgeon (double-tract reconstruction [17] or the double-flap technique [18]) (Fig. 2). All participating surgeons need to have performed at least 30 robotic gastrectomies before enrolling patients into the study, and at least 10 of these procedures need to have used the specific type of reconstruction technique (e.g., double-flap reconstruction after proximal gastrectomy) that the patient will receive. Details of the reconstruction techniques are determined by the surgeon. Patients will undergo standard postgastrectomy care at each institution during their hospital stays. A feeding jejunostomy can be placed for postoperative nutritional support at the surgeon’s discretion. These surgical procedures can be performed with a laparoscopic or robotic approach. Patients who undergo conversion to open laparotomy will be excluded from the study analyses, since conversion is expected to impact postoperative recovery. Patients who are found to have metastatic disease during surgery will also be excluded from the study analyses, regardless of whether the patient completed gastrectomy or not. Those excluded from the study analyses will be considered screening failures to allow for additional enrollees to meet the accrual target.

**Fig. 2 Fig2:**
[figure not shown]
Techniques of reconstructions after total and proximal gastrectomy

